### Randomisation

Randomisation is in permuted blocks stratified by collaborating centre, age and severity of X(T) as measured by the NCS. A blocked allocation (permuted random blocks of variable length) system is being used to allocate patients to the two groups in a 1:1 ratio to intervention (surgery) and control (active monitoring) groups. Randomisation is administered using a centralised, password-protected web-based system, which is managed by the Newcastle Clinical Trials Unit (NCTU). The PI at site, or individual with delegated authority, enters the patient ID, initials and the stratifying variables, which then return the allocation status. Participants are informed of their group allocation and given the appropriate Group Allocation Information sheet.

### Allocation concealment

Since surgery is the intervention of interest it is not possible to mask participants or parents to their group allocation. Masking of investigators is being achieved by the designation of a treatment orthoptist (TO) and a RO at each site. TOs cannot be masked to the group allocation of participants since they will conduct all assessments other than the outcome assessment and deal with queries from parents/children during the course of the trial. Clinical examination at the primary outcome visit will be carried out by the ROs who will be unaware of treatment group allocation. At this final study visit, the success of the masking will be assessed by asking the outcome assessor: “Do you think the patient has had surgery or not? Why do you think this?” Their responses will be recorded on a separate form.

### Proposed outcome measures

For children with X(T), and their parents, the most relevant outcome from intervention is the restoration of normal eye alignment, with associated cosmetic and functional benefits. The primary outcome in a full-scale trial will therefore be the difference in the cure rate of X(T) between the surgical and actively monitored group; this is also the primary outcome for which data will be collected in the current pilot in order to inform sample size calculations for a definitive RCT. Cure will be defined as:

• a control score (NCS) of 0 (misalignment never noticed by parents, no observable deviation on cover test)

• demonstrable near stereoacuity in children over 3 years of age

Secondary outcomes include age-specific QOL assessments, median scores of control of exotropia assessed by parental report and clinical components of the NCS and the Mayo Score, rates of amblyopia, use of health-care resources, NHS costs, costs to families accessing the treatments being evaluated and incremental cost per cured patient (with cure as defined by the primary outcome), and a cost-consequences analysis based on the incremental cost with respect to changes in all relevant outcomes where possible.

The key outcomes of this pilot study are:

• data on the variability of the primary and secondary outcome measures;

• rates of participant recruitment and randomisation;

• nature and extent of participation bias;

• rates of cross-over and retention of recruited participants;

• nature and extent of biases arising from cross-over or loss to follow-up.

An initial recruitment rate of >60% and a retention rate of >70% will be considered necessary to indicate feasibility of a full-scale RCT.

Our intention in the full trial would be to conduct a cost-effectiveness analysis based on incremental cost per cured patient (as defined by the primary outcome) and a cost-consequences analysis based on incremental cost with respect to changes in all relevant outcomes where possible, including the QOL measure and different clinical measures. In the pilot study, we will rehearse this cost-effectiveness analysis to inform the study hypothesis and the analysis plan for the definitive trial. We will also assess the ease of collecting information on outcome and costs needed for the health economics analysis.

With respect to collecting costs data, we will pilot the TTQ and HSUQ that capture patient costs and the NHS costs. We will assess the response and completion rates of these instruments. Patient costs will include travel costs for accessing NHS primary and secondary care; time costs of travelling and attending NHS primary and secondary care; and self-purchased health-care and related management costs. NHS costs will comprise use of health-care resources in both primary and secondary care. Total costs consisting of patient costs and the NHS costs will be compared between the randomised interventions.

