### Clinical tests

The following routine clinical assessments are undertaken at each visit:

• Binocular single vision (BSV) testing − either stereovision or motor fusion (reflex convergence of the eyes in response to a base out prism);

• Best corrected visual acuity (VA) on an age-appropriate test;

• Measurement of the ocular misalignment using the Alternate Prism Cover Test (APCT);

• Measurement of how well the squint is controlled using the revised Newcastle Control Score (NCS)
[36] and the Mayo score
[37]. The NCS combines an estimate of observed frequency of the X(T) by parents (home control) with an assessment of the child’s ability to realign the eye following a cover test to induce misalignment (clinic control for distance and near fixation) − possible total NCS scores range from 0–9 (0–3 for home, 0–3 for clinic distance and 0–3 for clinic near control). On the Mayo score, the distance score (0 to 5) is combined with near score (0 to 5) to yield an overall control score ranging from 0 to 10. On both instruments, higher scores are indicative of poorer control.

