#### Primary outcome visit

The final assessment (9-month outcome) will be conducted by a research orthoptist (RO) who is masked to the allocation of the child and has not otherwise been in contact with children enrolled in the study. The parent and child will be requested not to reveal the group allocation of the child to the RO prior to the assessment. While children have noticeably red eyes immediately following eye muscle surgery, it is recognised that this redness resolves within 6 weeks when this is a first procedure. Residual scarring of the conjunctiva following eye muscle surgery will be inconspicuous by 6 months.

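### Cure requires a zero home-control score from parents who know the allocation, so unequal parental reporting could veto cure unequally between arms with identical masked findings

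*Protocol article*

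**What the plan says.** Under Proposed outcome measures, cure has two parts. The first is "a control score (NCS) of 0 (misalignment never noticed by parents, no observable deviation on cover test"; the second is "demonstrable near stereoacuity in children over 3 years of age". The difference in cure rate between arms is named as the primary outcome of a full trial and is collected in the pilot to help size that trial. It also defines the cost per cured patient that the pilot rehearses.

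Under Clinical tests, one component of the NCS is "an estimate of observed frequency of the X(T) by parents (home control". The scoring is "0–3 for home, 0–3 for clinic distance and 0–3 for clinic near control", giving a total of 0 to 9.

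On masking, Allocation concealment states that "it is not possible to mask participants or parents to their group allocation", and that "Clinical examination at the primary outcome visit will be carried out by the ROs who will be unaware of treatment group allocation". Primary outcome visit says the final assessment is "conducted by a research orthoptist (RO) who is masked to the allocation of the child". The check on masking is a question put to that assessor about whether the child has had surgery.

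The parental and clinical parts of the NCS appear separately only as secondary outcomes, summarised as median scores.

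**The concern.** The NCS components are non-negative, so a total of 0 needs every component at 0. A single non-zero parental answer rules out cure, however good the masked examination. The protection against biased assessment is a masked orthoptist, but the item with this veto comes from people who know which treatment the child received.

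If parents in the two arms report differently for the same degree of deviation, the cure rates will differ for a reason unrelated to eye alignment. Those rates feed the sample size and endpoint choice of the definitive trial and the rehearsed cost per cured patient. The fourth pilot objective in the Background is to rehearse masking and outcome measurement, so how far the endpoint depends on unmasked report is a question this pilot is well placed to examine.

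**Working it through.** The article gives no cure rate, effect size or power calculation for cure, so there is no figure to reproduce. The check is first logical and then illustrative.

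**Logic**
1. Cure needs home = 0, clinic distance = 0, clinic near = 0 and, over age 3, near stereoacuity.
2. The home item comes from parents, who are unmasked. The clinical examination is done by the masked orthoptist.
3. The masking check questions the orthoptist only.
4. The home item is therefore an unmasked veto on cure among children who pass everything masked.

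**Model**
Let c be the proportion passing all masked components, and h the proportion with home = 0 among those who pass. Then P(cure) = c × h. With S for surgery and M for monitoring, the difference splits exactly:

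cS·hS − cM·hM = hS(cS − cM) + cM(hS − hM)

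The second term is the part due to unequal home scores. It scales with the masked pass rate under monitoring. With equal pass rates it is the whole difference: c × (hS − hM).

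**Illustration**
All rates are assumed: equal c in both arms, and hS = 0.9.

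| c | Cure, surgery (h = 0.9) | Cure, monitoring (h = 0.8) | Gap | Cure, monitoring (h = 0.6) | Gap |
|---|---|---|---|---|---|
| 5% | 4.5% | 4.0% | 0.5 points | 3.0% | 1.5 points |
| 10% | 9% | 8% | 1 point | 6% | 3 points |
| 30% | 27% | 24% | 3 points | 18% | 9 points |
| 50% | 45% | 40% | 5 points | 30% | 15 points |

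Reversing the assumed direction reverses the sign and leaves the size unchanged. With hS = hM the gap is 0.

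**Against the pilot's precision**
The Abstract's target of 120 retained gives 60 per arm at 1:1. Take c = 40% with h = 0.9 versus 0.7:
- Cure is 36% versus 28%, a gap of 8 points.
- The standard error of that difference is √[(0.36 × 0.64 + 0.28 × 0.72)/60] = 0.085, or 8.5 points.
- The chance of p < 0.05 (two-sided) is about 15%.

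A reporting gap of this size would usually not stand out from sampling error in the composite result, yet it would still enter the rates carried forward.

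**Whether the planned summaries would show it**
Median component scores by arm do not give the proportion of children who pass all masked components together. Nor do they give how often the home item alone blocked cure.

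**The case against.** Several counter-arguments carry weight.

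- **The article does not claim a fully masked primary outcome.** It says openly that parents are unmasked and applies masking to the clinical examination. A reader might infer a contradiction or a false claim of masking; the text does not support that. This is a disclosed limitation whose consequence for the endpoint is not followed through.
- **Home report has clinical value.** The deviation is intermittent, and the Background says it tends to show with fatigue, inattention or strong light. A non-zero home score beside clean clinic scores may be real squint that one visit missed. It would be wrong to call the whole home/clinic gap spurious, or to say that a masked-only cure separates bias from effect.
- **Parents can only veto.** A reader might infer that parental perception alone could produce cures. It cannot, because the masked items must also pass.
- **Direction and size are not in the documents.** It is tempting to say the arms have opposite incentives, but the article encourages parents generally to report concerns and gives no evidence of differential reporting. Entry requires an NCS of at least 3 and at least 15 dioptres of deviation, so the masked pass rate under monitoring may be low, which shrinks the effect.
- **Unmasking through the history.** A reader might infer that taking the home history at the final visit reveals the allocation to the orthoptist. The article does not say who takes it or when, and the visit schedule figure is not available. This is not relied on.
- **Secondary outcomes and the analysis plan.** Parental and clinical scores are reported separately, and the Mayo score as described has no home item. A clinic-only analysis may also stand in an analysis plan not shown, so its absence is not counted as an omission. What stands is that the article fixes a definition of cure with an unmasked veto, and that the median scores it names cannot recover the joint masked result.
- **The pilot is unpowered for cure,** and its feasibility thresholds concern recruitment and retention. This limits the harm to what is carried into the definitive trial.

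**Conclusion.** The point holds as an exposure to bias, not as a demonstrated bias or an internal contradiction. An unmasked item can veto the primary outcome, outside the protection of the masked orthoptist and the masking check. Unequal reporting could therefore produce different cure rates in arms with identical masked findings.

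The possible gap is about 0.5 to 15 percentage points. That range rests wholly on three assumptions: equal masked pass rates of 5% to 50%, home-zero rates of 90% versus 60% to 80% among children who pass, and the whole home difference being due to reporting. To the extent that the home difference reflects real deviation, the artefact is smaller. The consequence falls on the rates, endpoint and cost per cure taken into the full trial, not on the pilot's feasibility criteria.

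**What to change.** Keep the composite as the primary definition of cure. Pre-specify beside it:

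1. a masked-components cure (clinic distance = 0, clinic near = 0, and near stereoacuity where it applies), with rate and confidence interval by arm;
2. the distribution of the home score by arm among children who meet that masked definition.

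Use both versions when choosing the endpoint and sample size of the definitive trial. State in advance that home/clinic disagreement mixes reporting bias with true intermittent deviation missed at one visit, so it is descriptive and not an estimate of bias. Numbers will be small: with 60 per arm, a 40% pass rate leaves 24 children per arm in the second table, and a 5% rate leaves 3.

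The cost is one extra analysis of data already collected, with no change to treatment, visits or staff. The downside is that the masked-only version may miss deviation seen only at home, which is why it should sit beside the composite and not replace it.

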**Methods:**

Design: an external pilot patient randomised controlled trial.

Setting: four UK secondary ophthalmology care facilities at Newcastle NHS Hospitals Foundation Trust, Sunderland Eye Infirmary, Moorfields Eye Hospital and York NHS Trust.

Participants: children aged between 6 months and 16 years referred with suspected and subsequently diagnosed X(T). Recruitment target is a total of 144 children over a 9-month period, with 120 retained by 9-month outcome visit.

Randomisation: permuted blocks stratified by collaborating centre, age and severity of X(T).

Interventions: initial clinical assessment; randomisation (eye muscle surgery or active monitoring); 3-, 6- and 9-month (primary outcome) clinical assessments; participant/proxy completed questionnaire covering time and travel costs, health services use and quality of life (Intermittent Exotropia Questionnaire); qualitative interviews with parents to establish reasons for agreeing or declining participation in the pilot trial.

Outcomes: recruitment and retention rates; nature and extent of participation bias; nature and extent of biases arising from crossover or loss to follow-up; reasons for agreeing/declining participation; variability of cure rates (to inform power calculations for a definitive RCT); completion rates of outcome measures.

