### Participants and sample size

Children aged between 6 months and 16 years referred to the clinics with suspected X(T) from community screening, general practice or other health-care professionals, and subsequently diagnosed with X(T), as well as existing patients fulfilling the eligibility criteria. The parent/guardian provides written informed consent for participation in the study prior to any trial-specific procedures.

A formal power calculation was not performed for this feasibility study. It is not powered to detect a clinically or economically meaningful difference in the primary outcome between the surgical and active monitoring groups. Rather, the aim is to provide robust estimates of the likely rates of recruitment and retention, and to yield estimates of the variability of the primary and secondary outcomes to inform power calculations for a subsequent full-scale RCT. We originally estimated that over a recruitment period of 6 months (subsequently extended to 9 months) across four centres, we would be able to approach 240 patients who met the entry criteria. From their responses we would be able to determine whether the study is acceptable to parents and consequently whether it is possible to recruit patients and follow them up. We would also be able to estimate attrition rates. By approaching 240 children/parents we would be able to estimate the recruitment rate with a standard error no larger than 3.3%. Assuming that half of these children are actually recruited, we will be able to estimate the 6-monthly attrition rate with a standard error no larger than 4.3%.

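### The pilot's recruitment figures are not reconciled: precision is worked out on half of 240 (120), the target is 144, and feasibility requires more than 60%

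*Protocol article*

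**What the plan says.** Four statements in the protocol article bear on how many children the pilot expects to recruit and how many it needs.

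- **Number approached** (Participants and sample size): "we would be able to approach 240 patients who met the entry criteria". The time frame is given just before: "We originally estimated that over a recruitment period of 6 months (subsequently extended to 9 months) across four centres". The 240 is not restated for the longer period.
- **Planning proportion** (same section): "Assuming that half of these children are actually recruited", and on that basis "we will be able to estimate the 6-monthly attrition rate with a standard error no larger than 4.3" per cent. For the recruitment rate itself the claim is that "we would be able to estimate the recruitment rate with a standard error no larger than 3.3" per cent.
- **Target** (Abstract, Methods): "Recruitment target is a total of 144 children over a 9-month period, with 120 retained by 9-month outcome visit".
- **Feasibility rule** (Proposed outcome measures): "An initial recruitment rate of >60% and a retention rate of >70% will be considered necessary to indicate feasibility of a full-scale RCT".

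The sample-size section also says that "A formal power calculation was not performed for this feasibility study", so these precision statements and the feasibility rule are the whole quantitative basis of the pilot.

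**The concern.** The only recruitment proportion used for planning is 50%, and the only recruitment criterion is more than 60%. The number 120 also plays two roles: in the sample-size section it is the number recruited, in the abstract the number retained from 144. A reader cannot tell which recruited base the investigators planned on, or whether the abstract's target is meant to satisfy the criterion.

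Recruitment is the first listed objective of the pilot, and this is the only numerical recruitment threshold in the article. Trial status reports that, early on, fewer eligible patients had agreed than predicted, without giving the predicted rate. If the final rate falls between 50% and 60%, one part of the article makes it look better than planned and another makes it a failure.

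**Working it through.** **Inputs.** 240 approached, 50% recruited, standard errors of at most 3.3% and 4.3% (Participants and sample size); 144 recruited and 120 retained (Abstract); more than 60% recruited and more than 70% retained (Proposed outcome measures).

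**1. The plan's own precision figures.** SE = √(p(1−p)/n), largest at p = 0.5.

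- Recruitment rate, n = 240: √(0.25/240) = 3.23%. This agrees with the stated bound of 3.3%.
- Attrition, n = 120 (half of 240): √(0.25/120) = 4.56%. This exceeds the stated 4.3%. On 120 children, 4.3% is reached at an attrition of about 33%, so the bound holds only if attrition is no higher than that.
- Attrition, n = 144: √(0.25/144) = 4.17%, which is within 4.3%. A worst-case bound of 4.3% needs n of at least 0.25/0.043² = 135.2, that is 136.

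**2. The recruitment figures side by side.**

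| Source | Recruited | As a share of 240 | More than 60%? |
|---|---|---|---|
| Sample-size assumption | 120 | 120/240 = 50.0% | No |
| Abstract target (pairing with 240 inferred) | 144 | 144/240 = 60.0% | No, by one child |
| Smallest passing count | 145 | 145/240 = 60.4% | Yes |

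The two recruited bases differ by 144 − 120 = 24 children. Retention in the abstract is 120/144 = 83.3%, comfortably above 70%.

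**3. Chance of meeting the recruitment criterion.** Exact binomial with n = 240. The current rule needs X ≥ 145; a rule of at least 60% needs X ≥ 144.

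| True recruitment rate | P(more than 60%) | P(at least 60%) |
|---|---|---|
| 50% | 0.0008 | 0.0012 |
| 55% | 0.052 | 0.067 |
| 60% | 0.475 | 0.528 |
| 65% | 0.939 | 0.954 |

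The 50% assumption lies 10 points below the mark, and 10/3.23 = 3.1 standard errors, so rounding does not explain the gap.

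**4. Sensitivity to the number approached.** The article does not restate 240 for nine months, so I varied it as an assumption. At a true rate of 50%, the chance of exceeding 60% is 0.011 with 120 approached (X ≥ 73), 0.0018 with 200 (X ≥ 121) and 0.00006 with 360 (X ≥ 217, where 360 = 240 × 9/6). The conclusion at 50% does not depend on 240 being exact. The one-child result does: with 239 approached, 144/239 = 60.3% passes.

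**5. Precision of the reported rate.** At 60% of 240 the half-width of the 95% CI is 1.96 × √(0.6 × 0.4/240) = 6.2 points.

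**The case against.** A sizing assumption, a recruitment target and a feasibility threshold are different things and may properly differ. The half is an input to one precision statement and is not declared as a forecast. Assuming fewer recruits than the target is cautious there, since 120 gives a larger standard error than 144. A threshold states what a full trial would need, and a true 50% rate failing a 60% threshold is what a threshold is for.

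Most of this stands. A reader might infer that the plan contradicts itself outright, so that performing exactly as planned would mean declaring a full trial infeasible. The article does not support that: recruiting 120 would itself miss the declared target of 144, so it is not performing as planned. Nor does the article ever state 144 of 240. The 240 was estimated for six months and the 144 is tied to nine. If 144 was derived as 60% of 240, target and threshold were meant to agree, and only the strict inequality separates them: one child, against a standard error of about 3.2 points.

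A reader might also object that the word initial leaves the window open, or that a negative verdict could not be told apart from a badly set threshold. The first is detail that an article can leave to the full protocol. The second overstates the harm, because the observed rate will be reported and can be judged directly, alongside the reasons for declining.

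The objection does not explain why attrition precision rests on 120 recruits when the target is 144. Caution does not account for it either, because on 120 the stated bound is not a worst case.

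**Conclusion.** The concern holds as a failure to reconcile figures within the article. The planning proportion (50%, 120 recruits), the target (144 recruits) and the necessary recruitment rate (more than 60%) are stated in three places without being brought together. Recruitment at the sample-size section's rate would almost surely fail the criterion: about 0.1% chance of passing with 240 approached, and about 1% even with 120. Meeting the target of 144 exactly would also fail, by one child, but only if 240 is its denominator, which is inferred. The attrition standard error is understated as a bound on the base it uses (4.6% against 4.3%), unless attrition is at most about 33%. The binomial figures assume independent decisions at a common rate.

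The retention criterion and the 3.3% precision claim are sound. The point is moderate: it affects how the feasibility verdict is read, not the conduct of the pilot or the data collected.

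**What to change.** - Use one set of numbers in the abstract, the sample-size section and the feasibility rule: 240 eligible children approached, 144 recruited, 120 retained (83%). If 144 has another denominator, state it.
- In the sample-size section, replace the assumption of half with the target of 144 and restate the attrition standard error on that base: at most 4.2%.
- Write the recruitment criterion as at least 60% of eligible children approached, so that the stated target meets it.
- Report the recruitment rate with its 95% CI, about ±6 points, next to the criterion.

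Do not lower the pass mark to 50% to match the planning assumption. Recruitment was already under way with lower uptake than predicted, and such a change would relax a prespecified criterion after seeing unfavourable data. Moving from more than 60% to at least 60% shifts the count by one child (145 to 144), and should be recorded as a dated clarification.

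The cost is a few sentences of wording. No extra patients, visits or data are needed.
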